## Abstract

**Background:**

Postpartum urinary retention (PUR) is a common and clinically relevant complication after delivery. Although urinary catheterization can provide temporary relief from voiding disorders, it is associated with discomfort, pain, potential urethral trauma, and an increased risk of urinary tract infection. Preliminary randomized and observational studies have suggested that acupuncture may facilitate voiding and early bladder recovery in PUR; however, the current evidence base remains limited by small sample sizes, heterogeneous methods, and risk of bias. To address these gaps, we designed a multicenter, randomized, sham-controlled clinical trial to evaluate whether electroacupuncture (EA) reduces the incidence of PUR and improves early bladder recovery.

**Methods:**

This is a multicenter, randomized, parallel-group clinical trial conducted in China to investigate the impact of EA intervention on the incidence of PUR. Patient screening and enrollment will take place at four hospitals in China: the First Teaching Hospital of Tianjin University of Traditional Chinese Medicine, Tianjin Central Hospital of Gynecology Obstetrics, Tianjin Shuige Hospital and Second People’s Hospital of Fengrun District, Tangshan City. Patients will be randomly assigned to either the EA group or the sham acupuncture group, with 330 patients in each group. Each acupuncture treatment will comprise three 30-min sessions over 2 days (the first hour, the first day, and the second day after delivery). The primary outcome measure is the incidence of PUR. Adverse events will be recorded, and their impact will be analyzed at the end of the trial.

**Conclusion:**

This multicenter, randomized, sham-controlled trial is designed to rigorously evaluate whether EA reduces the incidence of PUR and accelerates early bladder recovery. The findings will contribute evidence to inform the role of non-pharmacologic interventions in postpartum rehabilitation.

**Clinical trial registration:**

Chinese Clinical Trial Registry, ChiCTR2300078039.

## Introduction

1

Postpartum urinary retention (PUR) is a serious and common clinical complication after delivery (1), mainly manifested as voiding disorders or incomplete bladder emptying. Based on its different clinical manifestations, PUR can be classified into overt, covert, and persistent PUR. Overt PUR refers to the inability to void 6 or more hours after vaginal delivery or removal of catheter after cesarean section. Covert PUR is defined as post-void volume (PVR) of >150 mL measured by ultrasound or catheterization after spontaneous urination. Persistent PUR is urinary retention lasting beyond 3 days postpartum and requires indwelling catheter or intermittent self-catheterization (2, 3).

Based on differences in diagnostic criteria, measurement methods, and timing, the incidence of PUR varies from 1.5 to 45% (4). However, covert PUR is somewhat concealed, making clinical screening and management more challenging, and it is more prone to delayed diagnosis and misdiagnosis. Although some studies have shown that covert PUR can normalize within a few days, even a single over-distension of the bladder can cause long-term urination disturbance, affecting the long-term function of the bladder, leading to recurrent urinary tract infections, and even renal failure (5). Additionally, PUR can affect uterine involution, resulting in increased postpartum bleeding, which imposes a heavy psychological burden on the parturients and seriously impacts their physical and mental recovery, as well as their quality of life and long-term health (4). Therefore, early diagnosis and prevention of PUR are of great significance for the physical and mental well-being of parturients.

The clinical treatment of PUR mainly involves urethral catheterization, drug therapy, physical therapy, and pelvic floor muscle functional exercises (6). While urinary catheterization can temporarily alleviate the clinical symptoms of voiding disorders, it does not offer a complete cure. Additionally, this procedure can cause maternal discomfort, pain, and anxiety, and even urethral injury, increasing the risk of urinary system infections (7, 8). Studies have shown that urinary tract infections caused by urinary catheter account for approximately 60 to 80% of patients with urinary tract infections, and long-term indwelling urinary catheters can weaken bladder autonomic function, which is not conducive to recovery (8). Drug therapy, such as tamsulosin, neostigmine, and bethanechol, mainly acts on bladder and sympathetic nervous system receptors, and its impact on improving post-void residual bladder volume is unclear. Additionally, these drugs have side effects such as tachycardia, diarrhea, and vomiting, and it is unknown whether they are secreted in human milk, thus safety considerations for maternal breastfeeding are lacking (2). Conventional non-invasive methods, such as functional exercises and acupoint hot compresses, are easy to accept but have limited efficacy for patients with severe PUR or complications, and the long-term effect is unclear (8). Therefore, it is urgent to find a safe, effective, less side effect-prone, and long-term curative approach for the prevention and treatment of PUR.

Acupuncture is practiced internationally and, for selected indications, has been incorporated into some clinical practice guidelines; however, recommendations and the underlying evidence quality vary by condition (9). For urinary retention—particularly PUR—preliminary randomized and observational studies suggest that acupuncture, including EA, may facilitate spontaneous voiding and early bladder recovery (10). Yet existing data are constrained by small sample sizes, heterogeneous interventions and comparators, short follow-up, and risk of bias; high-quality multicenter, sham-controlled trials remain scarce, and important questions persist regarding covert PUR and longer-term outcomes. Taken together, these limitations necessitate a rigorously designed multicenter, randomized, sham-controlled trial to establish whether EA confers clinically meaningful benefits for PUR, including covert PUR and longer-term outcomes (11).

## Methods

2

### Study design

2.1

This is a multicenter, randomized, parallel-group clinical trial conducted in China to investigate the impact of EA intervention on the incidence of PUR. The study protocol is to prefer the Consolidated Standards of Reporting Trials (CONSORT) guidelines (12) and the Standards for Reporting Interventions in Clinical Trials of Acupuncture (STRICTA) (13), as well as with the Standard Protocol Items: Recommendations for Interventional Trials (SPIRIT) (14) statement the study will commence following ethics approval and registration protocol. Patient screening and inclusion will start in August 2024. It has been registered at Chinese Clinical Trials Registry (ChiCTR2300078039). Figure 1 is the study flow chart and Table 1 shows the schedule of enrolment, interventions and assessments.

**Figure 1 fig1:**
[figure not shown]
The study flow chart.

**Table 1 tab1:** Schedule of trial enrolment, interventions and assessments.

Period	Enrolment	Allocation	Treatment			Assessment				Follow-up	
Time points	Before delivery		1 h	24 h	48 h	the 1st urination	6 h	24 h	48 h	6–8 weeks	1 year
Enrolment											
Eligibility screen	X										
Informed consent	X										
Randomization		X									
Intervention											
Electro-acupuncture			X	X	X						
Sham acupuncture			X	X	X						
Assessments											
Postpartum urinary retention						X	X	X	X		
The time of first urination						X					
The amount of first urination						X					
The feeling of unobstructed first urination (TCM syndrome quantification scale)						X				X	
Effective rate of urination						X					
Postpartum uterine contraction pain (VAS)							X	X	X		
The amount of 24 h postpartum bleeding								X			
Postpartum depression and anxiety (EPDS)									X		X
Pelvic floor dysfunction questionnaire (PFDI-20)											X
Blindling									X		
Adverse events								X	X		

### Participants

2.2

#### Recruitment and withdrawal

2.2.1

Patient screening and recruitment will take place at four hospitals in China: the First Teaching Hospital of Tianjin University of Traditional Chinese Medicine, Tianjin Central Hospital of Gynecology Obstetrics, Tianjin Shuige Hospital and Second People’s Hospital of Fengrun District, Tangshan City. The target enrollment is set at 660 patients. Obstetricians responsible for identifying eligible patients will be briefed about the study, and these patients will then be given the option to decide whether they want to participate. After signing the informed consent form, patients will be randomly assigned to either the electro-acupuncture group or the sham acupuncture group, with 330 patients allocated to each group. It is important to emphasize that patients have the right to withdraw from the study at any stage.

#### Inclusion criteria

2.2.2

Patients meeting the following additional inclusion criteria may be included:Primiparous women aged 20 to 45 years with singleton pregnancies planning for vaginal delivery.Delivery at a gestational age of 37 to 42 weeks.Being clearly conscious and cooperative.Signing the informed consent.

#### Exclusion criteria

2.2.3

Patients meeting any of the following conditions will be excluded:Termination of pregnancy due to fetal malformation or stillbirth.Severe central nervous system diseases, internal and surgical diseases, mental and psychological diseases, urogenital-related diseases, infectious diseases, and long-term drug treatment.Severe coagulation disorders and a tendency towards spontaneous bleeding.Skin damage at the acupuncture site.Refusal to follow-up.Refusal to sign the informed consent form.

#### Drop-out and discontinuation criteria

2.2.4

All randomized participants will be included in the Intention-to-Treat (ITT) analysis. The Full Analysis Set (FAS) will be identical to the ITT population. Participants who meet any of the following protocol deviation criteria will be excluded from the Per-Protocol (PP) analysis but retained in the ITT/FAS. All participants who receive at least one session of acupuncture (active or sham) will be included in the Safety Analysis Set. Sensitivity analyses will be conducted to explore the impact of major protocol deviations.Rescue measures are implemented due to postpartum hemorrhage, eclampsia, or other obstetric conditions;Conversion from vaginal delivery to cesarean section.Infection is diagnosed during delivery;An indwelling catheter is used and diuretics are administered due to other diseases within 6 h after delivery;A degree III laceration above the perineal fissure is diagnosed;Due to other postpartum reasons, the number of treatment sessions received by patients is less than 3 times, which affects the analysis and judgment of the results;The researchers can terminate the patients from the study at any stage if any events occur that may affect the safety of patients in the study.

### Randomization and blinding

2.3

This study will use the network-based clinical trial public management platform (ResMan, http://www.medresman.org.cn/login.aspx) to implement centralized randomization. Randomization will be carried out using stratified block randomization (with block sizes of 4 or 6) according to the four participating research centers, and allocation concealment will be achieved through the central randomization system of the ResMan platform. After patients complete baseline assessments and are confirmed to be eligible, independent researchers will log into the system to obtain an unpredictable, automatically generated random allocation sequence. Group allocation information will be blinded to the study participants, outcome assessors (including personnel who perform BVI-9400 bladder scans, EPDS scoring, and other questionnaire assessments), and data analysts. To maintain blinding consistently across all study centers, these assessors will not be involved in any treatment-related activities and will receive standardized training on blinded assessment procedures. Furthermore, data entry will be performed by independent personnel who are not involved in patient recruitment or treatment delivery. The sham procedure uses non-penetrating needles and 0 mA current to mimic active treatment without physiological effects. At the end of the trial, the James Blinding Index will be used to quantitatively analyze the success degree of blinding. However, due to operational requirements, acupuncture therapists cannot be blinded.

After the final acupuncture treatment, all patients will be asked, “Do you believe that acupuncture has penetrated the skin?” The response will be categorized into three options:Acupuncture penetrated the skin;Acupuncture did not penetrate the skin;I do not know.

This will be taken into consideration to evaluate the success of blinding.

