**Figure 2 fig2:**
[figure not shown]
**(A)** Shows the specific location of the two groups of acupoints; **(B)** Shows the connection method of the EA apparatus; **(C)** Shows active acupuncture and sham acupuncture.

The sequence and technique of acupuncture are as follows: GV20 will be needled at a depth of 10–15 mm with an angle parallel to the scalp, followed by small-amplitude, high-frequency twirling (90°–180°, 100–120 rotations/min for 1 min). CV3 and CV4 will then be obliquely punctured at 10–20 mm with a 45° abdominal angle and manipulated with the same twirling parameters for 1 min. Practitioners will apply standardized manual stimulation per STRICTA to elicit characteristic needling sensations (e.g., aching, heaviness, distension)—terms traditionally referred to as “de qi”; this terminology is used in its historical context and does not imply a validated biomedical mechanism. To operationalize sensation intensity, participants will rate needling sensations using a 0–10 Numeric Rating Scale (0 = no sensation, 10 = strongest imaginable sensation) immediately after needle manipulation, and practitioners will record perceived needle grasp (present/absent). Paired electrodes from an EA device (SDZ-IIB, Suzhou Medical Appliance) will be attached to the CV3 and CV4 needles, set to continuous 2 Hz, with current intensity adjusted individually between 1 and 5 mA to produce visible, comfortable local muscle twitching without pain. Needles will be retained for 30 min. The procedure and electrode connections are shown in Figure 2.

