#### Sham acupuncture group

2.4.2

Patients in the sham group will receive a non-insertive procedure matched to the EA group for time, attention, body position, and device appearance. Stimulation will be delivered at three predefined non-acupoint sites labeled sham-Baihui, sham-Zhongji, and sham-Guanyuan. Blunt-tip telescopic sham needles (0.25 mm× 40 mm, Hwato, Suzhou, China) will rest on the skin through adhesive guide tubes without skin penetration; no manual twirling will be performed and practitioners will not aim to elicit characteristic needling sensations (traditionally termed “de qi”). Leads from an EA device (SDZ-IIB, Suzhou Medical Appliance, Suzhou, China) will be attached to the sham-Zhongji and sham-Guanyuan simulators with the device powered on but current set to 0 mA (no output). The simulators will remain in place for 30 min, with the number and schedule of sessions identical to the EA group. Specific procedures are summarized in Table 3 and Figure 2.

**Table 3 tab3:** Locations and needling methods of non-acupoints for Sham group.

Acupoint	Location	Needling method
Sham-Baihui	2 cun lateral from GV20	Sham needles will not penetrate the skin
Sham-Zhongji	6 cun lateral from CV4(left)	Sham needles will not penetrate the skin
Sham-Guanyuan	6 cun lateral from CV4(right)	Sham needles will not penetrate the skin

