### Statistical analysis

2.10

Demographic characteristics, general situations, and baseline conditions of the two groups will be compared and analyzed. For measurement data, an independent samples t-test or Wilcoxon rank-sum test will be employed, while χ^2^ test or Fisher test will be used for categorical data.

The incidence of PUR will be accurately assessed using Fisher’s exact test, and the relative risk (RR) along with the corresponding 95% confidence interval will be calculated. For other ordinal data, the Wilcoxon rank-sum test will be applied, while clinical counting data will undergo testing through the χ2 test. Postpartum depression and anxiety will be compared using Fisher’s exact test, and the RR along with the corresponding 95% confidence interval will be computed. Subject blinding effectiveness will be analyzed using the James Blinding Index. All statistical tests will be two-sided, and a *p* value less than 0.05 will be considered statistically significant for the tested differences.

For exploratory subgroup analysis, participants will be stratified into different subgroups based on age (< 40 years, ≥ 40 years), BMI (< 25 kg/m^2^, ≥ 25 kg/m^2^), duration of labor (< 700 min, ≥ 700 min), epidural anesthesia (with or without), vaginal midwifery techniques (forceps midwifery, fetal head attraction midwifery, fetal head rotation, perineotomy), gestational age (> 280 days, ≤ 280 days), and newborn birth weight (< 4,000 g, ≥ 4,000 g). The incidence difference between the two groups will be compared within each subgroup using the same statistical methods as mentioned above.

The primary analysis will follow the intention-to-treat (ITT) principle. Missing data will be handled using multiple imputation. A logistic regression model adjusting for study center will be used for the primary outcome. Secondary and subgroup analyses will apply Bonferroni correction for multiple comparisons.

GraphPad Prism 10.2 will be used for all statistical analysis.

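### The only blinding statistic named, the James index, cannot show which arm is unblinded and can look reassuring when many sham women are unsure; arm-specific results should be reported beside it

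*Protocol article*

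**What the plan says.** The choice of index is stated twice in the protocol article. Section 2.3 (Randomization and blinding) says that "the James Blinding Index will be used to quantitatively analyze the success degree of blinding". Section 2.10 (Statistical analysis) says: "Subject blinding effectiveness will be analyzed using the James Blinding Index". No other blinding index and no summary by arm is named.

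The data come from one question put to all women after the last session: "Do you believe that acupuncture has penetrated the skin". There are three possible answers: penetrated, and the two listed as "Acupuncture did not penetrate the skin;I do not know". Section 2.3 then adds: "This will be taken into consideration to evaluate the success of blinding".

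The two procedures feel different by design. In the EA group needles are inserted and twirled, and the current is adjusted "to produce visible, comfortable local muscle twitching without pain" (section 2.4.1). In the sham group nothing penetrates the skin, there is no twirling and the output is 0 mA (section 2.4.2). The target is 660 women, "with 330 patients allocated to each group" (section 2.2.1).

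**The concern.** The James index gives a right guess weight 0, a wrong guess weight 0.5 and a do-not-know answer weight 1, and pools both arms into one number. Two consequences follow. It cannot say which arm has identified its treatment. And a large do-not-know share in one arm raises the value whatever happens in the other.

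The second matters here because the sensory cues are unequal. EA women have strong grounds to say that the needle went in, while sham women may well be unsure. The feeling at first urination, VAS pain and EPDS are self-reported. If EA women are confident and sham women are not, expectation could contribute to differences on these outcomes, and the named statistic might not reveal it.

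**Working it through.** The article gives no blinding figure or threshold, so there is nothing to reproduce. The check compares the two indices on the same tables.

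**Inputs.** From the article: three answer options, asked of all women, 330 per arm. Assumed: the answer distributions, which the article does not give. The index definitions are the standard ones.

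**Formulas.**
- James = [1 + P_DK + (1 − P_DK) × K] / 2, with K = (P_Do − P_De) / P_De. P_DK is the overall do-not-know share. P_Do and P_De are the observed and chance-expected weighted disagreement among women who guessed.
- Bang, per arm = (right − wrong) / n. Do-not-know answers stay in n.

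Reference point: if everyone guesses 50/50, P_DK = 0 and K = 0, so James = 0.50. Pure guessing with 10% unsure gives (1 + 0.10)/2 = 0.55.

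**Step 1: can James tell the arms apart?** Answers are penetrated/not/do not know.

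- *EA alone unblinded*: EA 297/16/17, sham 110/110/110. P_DK = 127/660 = 0.192; 533 women guessed, 126 wrongly. P_Do = 0.5 × 126/533 = 0.118. P_De = 0.5 × (313 × 126 + 220 × 407)/533² = 0.227. K = −0.479. James = (1 + 0.192 − 0.808 × 0.479)/2 = **0.403**. Bang: EA +0.85, sham 0.00.
- *Sham alone unblinded* (mirror image): EA 110/110/110, sham 16/297/17. The do-not-know total, the wrong total and the cross-products are unchanged, so James = **0.403**. Bang: EA 0.00, sham +0.85.
- *Both moderately unblinded*: 60/20/20% right/wrong/unsure in each arm. P_DK = 0.20, P_Do = 0.125, P_De = 0.25, K = −0.5. James = (1.20 − 0.40)/2 = **0.400**. Bang: +0.40 in both.

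Three different situations give practically one James value. The equality of the first two holds for any answer distribution under 1:1 allocation.

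**Step 2: can James look reassuring when the EA arm has identified its treatment?** EA 264 right, 16 wrong, 50 unsure (80/5/15%); sham 66/66/198 (20/20/60%). P_DK = 248/660 = 0.376; 412 guessed, 82 wrongly. P_Do = 0.5 × 82/412 = 0.0995. P_De = 0.5 × (280 × 82 + 132 × 330)/412² = 0.196. K = −0.492. James = (1.376 − 0.624 × 0.492)/2 = **0.534** (bootstrap limits about 0.50 to 0.57), close to the 0.55 of pure guessing with 10% unsure. Bang: EA (264 − 16)/330 = +0.75, sham 0.00.

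**Step 3: how far does Step 2 depend on the sham do-not-know share?** Same EA pattern, the remaining sham answers split evenly:

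| Sham women unsure | James |
|---|---|
| 0% | 0.34 |
| 20% | 0.40 |
| 40% | 0.47 |
| 50% | 0.50 |
| 60% | 0.53 |

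The reassuring reading needs about half or more of the sham arm to be unsure.

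**Step 4: what does a high EA value mean?** The question is about skin penetration, so a convincing sham makes both arms say that it penetrated. With 297/16/17 in both arms, Bang is +0.85 in EA and −0.85 in sham (James 0.526). The same EA value of +0.85 beside a sham value of 0.00 (Step 1) means something else: the arms hold unequal beliefs. The EA value must be read with the sham value.

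**The case against.** The James index is an accepted method that suits a three-option answer set, so naming it is neither an error nor a contradiction. The article condenses a fuller protocol, an analysis plan not shown could add results by arm, and the sentence on taking the answers into consideration does not confine the evaluation to the pooled value. All of this stands and keeps the point small. It does not remove it: the method is stated in two sections, and each time only the pooled index is named.

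A reader might infer that the index averages one-sided unblinding away altogether. Step 3 shows otherwise: it falls to 0.34 to 0.47 when 0 to 40% of sham women are unsure, so it can signal that something is wrong, though not where. A reader might also infer that a high EA value proves failed blinding. Step 4 shows that it does not on its own.

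Nor does the article support a claim that the primary result is put at risk by this choice. No decision rule or analysis uses the index. Covert retention is measured by bladder scan by blinded operators, with a second blinded reading at 150 mL or more (section 2.5.1). A different index would describe the difference in sensation between the procedures but would not reduce it.

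**Conclusion.** The point holds in a limited form. As the only named blinding statistic, the James index cannot show which arm is unblinded (0.403, 0.403 and 0.400 for EA-only, sham-only and two-arm unblinding). It can also stand at or above 0.5 despite strong EA-arm identification once about half or more of sham women are unsure (0.534 in the example). The answer patterns are assumptions; that swapping the arms leaves the index unchanged is not. The consequence is confined mainly to interpreting the self-reported secondary outcomes, and no effect estimate changes. Low severity, worth doing because it is nearly free.

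**What to change.** In section 2.10, and to match in section 2.3, state that the three-option answers will be reported as a 2x3 table by arm, with the Bang index and its 95% CI for EA and for sham, and that the blinding conclusion rests on the two arm values read together. A high EA value with an equally negative sham value means that both arms believed the needle penetrated, so the sham was convincing. A high EA value with a sham value near zero means unequal expectation, to be borne in mind for the self-reported outcomes. The James index stays as a supplementary figure.

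The cost is a line or two of analysis wording. No new question, visit or patient is needed.

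Precision is ample at 330 per arm. With variance [p(1 − p) + q(1 − q) + 2pq]/n for right share p and wrong share q, the Step 2 EA arm (p = 0.80, q = 0.048) has variance 0.284/330 and standard error 0.029, so +0.75 has 95% limits of about 0.69 to 0.81. The sham arm (p = q = 0.20) has variance 0.40/330 and standard error 0.035, so 0.00 has limits of about −0.07 to +0.07.

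### The only blinding question described asks about skin penetration, once, after the third session, so a James index based on it measures belief about penetration rather than about allocation

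*Protocol article*

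**What the plan says.** Section 2.3 (Randomization and blinding) fixes the wording, answers and timing of the participant item. "After the final acupuncture treatment, all patients will be asked": "Do you believe that acupuncture has penetrated the skin". The answers are "Acupuncture penetrated the skin;Acupuncture did not penetrate the skin;I do not know". The section says the response will be considered in judging whether blinding succeeded. Table 1 marks blinding once, in the 48 h column.

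For the analysis, section 2.10 states: "Subject blinding effectiveness will be analyzed using the James Blinding Index". Section 2.3 names the same index. No other participant item and no arm-specific index is described.

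The arms differ in more than penetration:

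- **Electroacupuncture (2.4.1).** Needles are twirled to elicit sensation, "participants will rate needling sensations using a 0–10 Numeric Rating Scale", and the device is set "with current intensity adjusted individually between 1 and 5 mA to produce visible, comfortable local muscle twitching without pain".
- **Sham (2.4.2).** The procedure is described as "matched to the EA group for time, attention, body position, and device appearance", but "no manual twirling will be performed", no needling sensation is sought, and the device output is 0 mA.

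**The concern.** A blinding check should ask what a woman believes about her allocation. This one asks about a single physical feature of the needle. A woman in the sham arm who feels no tingling and sees no twitch may work out her arm, yet still answer that the needle penetrated because the blunt tip pressed on her skin. An index built on that answer counts her as a wrong guess, which moves it towards successful blinding.

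Timing adds a second problem. Section 2.4 calls the first 6 to 12 hours the critical window for onset of retention. By the time the question is asked, women know how they voided over the first day, so the answer can partly reflect outcome. Nothing is recorded about belief after the first session.

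Contraction pain, smoothness of urination and the EPDS are self-reported and open to expectation. An index that looks satisfactory for the wrong reason would make it harder to separate an expectation effect from an effect of electroacupuncture on those outcomes.

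**Working it through.** The plan gives no expected answers and no target value for the index, so there is no stated figure to reproduce. The check has three steps.

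**1. What differs and what is asked (sections 2.3, 2.4.1, 2.4.2)**

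| Feature | Electroacupuncture | Sham | Asked about? |
|---|---|---|---|
| Skin penetration | yes | no | yes |
| Twirling | yes | no | no |
| Sensation deliberately elicited | yes | no | no |
| Current | 1 to 5 mA, to visible twitch | 0 mA | no |
| Believed allocation | n/a | n/a | no |

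**2. Timing (Table 1; sections 2.5.1, 2.5.2.3, 2.5.2.5)**

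- Before the question: first void, 6 h and 24 h assessments.
- At or after about the same time: the day-2 retention check (same 48 h column), the last pain VAS (2 h after the second-day session) and the first EPDS (after the final session).

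**3. How the James index behaves on this item**

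Index = [1 + P + (1 − P)K]/2, where P is the proportion answering do not know and K = (observed − expected disagreement)/expected disagreement among the rest. A value of 0 means all correct, 0.5 chance guessing, and 1 all do not know. In the electroacupuncture arm the correct answer is penetrated; in the sham arm it is not penetrated. The arms are equal in size, and the splits below are assumptions per 100 women.

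*Everyone answers penetrated.* P = 0. Observed disagreement is 100/200 = 0.5 and expected is 0.5, so K = 0 and the index is (1 + 0 + 0)/2 = 0.50. This holds whatever the women believe about their arm.

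*Electroacupuncture 80/5/15, sham 50/20/30 (penetrated / not / do not know).*
- P = 45/200 = 0.225, leaving 155 women who gave a view.
- Observed disagreement = (5 + 50)/155 = 0.3548.
- Expected = (85/155)(25/155) + (70/155)(130/155) = 0.4672.
- K = (0.3548 − 0.4672)/0.4672 = −0.2405.
- Index = [1 + 0.225 + 0.775 × (−0.2405)]/2 = 0.519.
- Bang index: electroacupuncture (80 − 5)/100 = 0.75; sham (20 − 50)/100 = −0.30.

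*Range, holding electroacupuncture at 80/5/15:*

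| Sham split | James | Bang, sham |
|---|---|---|
| 80/5/15 | 0.58 | −0.75 |
| 60/15/25 | 0.54 | −0.45 |
| 50/20/30 | 0.52 | −0.30 |
| 40/40/20 | 0.40 | 0.00 |
| 20/50/30 | 0.35 | 0.30 |

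For contrast, suppose women were asked their allocation and many recognised the current. Answers of 80/5/15 and 10/70/20 (electroacupuncture / sham / do not know) give 0.25, and all correct gives 0.00. These are illustrations, not predictions.

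**The case against.** **The link from question to index is inferred.** Section 2.3 says the answer will be taken into consideration; it does not say the James index is computed from this item alone, and the full protocol and case report form are not shown. This stands as a caveat. The item is nonetheless the only one described, and its wording, answers and timing are all fixed.

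**The figures depend on chosen splits.** This also stands. When more sham women notice non-penetration the index falls to 0.35 to 0.40, so the item is not blind to unblinding. The case with everyone answering penetrated needs no judgement about current, but it is an extreme.

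**The blind may be sound.** A reader might infer that the current must give the arm away. The documents do not support that: each woman sees only her own procedure, what women are told to expect is not shown, and calling current the main cue is an inference. A Bang index of 0.75 with −0.30 means that women in both arms mostly believed they had penetrating needles, which does not by itself show a failed blind.

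**The item is not last in the sequence.** A reader might take it to follow every in-hospital outcome. It does not: the last VAS and the first EPDS come after the final session, and the day-2 retention check shares the 48 h column.

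**The consequence is limited.** Residual volume is scanned by blinded assessors, with a blinded recheck of values of 150 mL or more, and no stated analysis depends on the index. This is fair, and it is why the point ranks as an improvement rather than a fatal flaw.

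**Conclusion.** The point holds in a limited form. The stated item measures belief about penetration, while the arms also differ in twirling, elicited sensation and current. A James index computed from it is 0.50 if all women answer penetrated, whatever they know about their arm. Under the assumed splits it ranges from about 0.35 to 0.58, driven by how many sham women notice non-penetration. A value near 0.5 would therefore not show that allocation was concealed. The single question at 48 h also leaves belief during the first day unmeasured.

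This rests on the item feeding the index, which the text implies but does not state, and on assumed answers.

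Two stronger readings are not supported. The documents contain nothing to show that the blind has failed. Nor do they show the sham to be misdescribed: the matching claimed is for time, attention, position and device appearance, and the absence of twirling and current is stated openly. Redesigning the sham procedure does not follow from this point, and changing it part-way could mix two control procedures.

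**What to change.** Add a believed-allocation question (electroacupuncture, sham or do not know) with a short free-text reason. Ask it after the final session and preferably also once shortly after the first. Compute the blinding index from this question, and report the Bang index for each arm beside the James index. The penetration item can stay as supporting information.

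The cost is one or two case report form items. The main drawback is that an early question may prompt some women to think about their allocation; if that is judged too risky, the question after the final session alone still corrects what is measured, though not when.
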